**Figure 1 F1:**
[figure not shown]
Flow chart of the trial.

The arrangements for enrollment during hospitalization and outpatient follow-up after discharge are shown in Table 1. At the beginning of the study, all eligible newborns will undergo a detailed physical examination. The pediatrician will record comprehensive general information (including the mother's prenatal examination, fetal condition, birth history, medication history, feeding history, length, weight, etc.). Jaundice indicators will be recorded before enrollment, blood samples will be collected (for thyroid function and serum bilirubin), and any adverse events will be documented.

**Table 1 T1:** Enrollment and follow-up items during hospitalization and after discharge.

Inspection schedule									
Time window	Enrollment, D0	Phototherapy for 12 h, D1	Rest for 6–8 h after phototherapy, D1	Phototherapy for 12 h, D2	Rest for 6–8 h after phototherapy, D2	Phototherapy for 12 h, D3	Rest for 6–8 h after phototherapy, D3	On the day of discharged, D4	Post-discharge, D10, D20 and D30
Informed consent	X								
Inclusion and exclusion criteria	X	X	X	X	X	X	X	X	X
Feeding situation	X	X	X	X	X	X	X	X	X
Give light therapyintervention		X		X		X			
Random givento probiotics		X		X		X		X	X
check-up	X	X	X	X	X	X	X	X	X
vital sign	X	X	X	X	X	X	X	X	X
Weight/urine output	X	X	X	X	X	X	X		X
Serum examination 1		X							
Systemic assessment	X	X	X	X	X	X	X	X	X
Percutaneous bilirubin determination	X	X	X	X	X	X	X	X	X
Stool assessment andSystemic assessment		X		X		X		X	X

The investigator will re-check the inclusion/exclusion criteria on the first day, perform patient management, conduct detailed physical and serologic examinations prior to phototherapy, and record the adverse events described in Table 1. They will collect stool and blood samples from the subjects. Subjects will receive the first 12 h of phototherapy and the assigned probiotics before phototherapy. After 12 h of phototherapy, researchers will observe phototherapy-related side effects (including body temperature, rash, stool frequency and shape, etc.), record information, collect stool samples, and measure TCB. On the next day, after 6–8 h of rest, the infant will receive a second 12 h phototherapy session while the assigned probiotics are orally administered, and the researchers will again assess and collect fecal samples. The same process will be followed for the third day, and if necessary, subjects may continue with the fourth and fifth 12 h phototherapy sessions, with at least 6 h of rest after each phototherapy session. Stool collection will still be required after each phototherapy session. Subjects will not require further phototherapy and will be discharged once they meet the discharge criteria.

Upon meeting the discharge criteria, the investigator will perform subject management, a detailed physical examination, serological testing, and evaluation of adverse events prior to discharge. Study follow-up on days 10, 20, and 30 will be completed at the outpatient follow-up for hyperbilirubinemia, during which stool and related data will be collected. Infants in the experimental group will continue to receive their assigned oral probiotics during hospitalization after enrollment and during outpatient follow-up for one month.

Stool samples weighing 500 mg and blood samples measuring 0.5 microliters were collected from each subject. The stool samples will be stored at −80°C after freezing, while the blood samples will be tested immediately. There would be no restrictions on the feeding patterns of both the experimental and control groups during the study. Parents are allowed to freely choose between breastfeeding, artificial feeding, and mixed feeding.

### Endpoints

(1)Primary endpoint: significant reduction in the incidence of clinical side effects (i.e., diarrhea, rash, fever, vomiting, convulsions, feeding intolerance, etc.).(2)Secondary endpoints: after the addition of probiotics, the intestinal flora will be maintained in a stable state after phototherapy, and the changes in metabolic indicators; changes in jaundice (i.e., serum bilirubin, bile acid and transcutaneous bilirubin data), feeding status, changes in urine volume and weight, and vital signs during phototherapy

### Participant timeline

The schedule of enrollment, intervention, assessment, and follow-up of the subjects is shown in Table 1.

### Sample size

In previous clinical trials investigating the effects of probiotics on phototherapy, it was observed that the use of probiotics reduced the incidence of digestive tract side effects caused by phototherapy. Based on the results of a literature review, it was found that the general incidence of such side effects is approximately 47%, and our goal is to reduce this incidence to about 10% by adding the appropriate combination of probiotics. To achieve this goal, a margin of 0.05 was assumed, with a type I error of 0.05 and a power of 0.8. Using a difference test for two-sample ratios, a sample size of 20 cases per group was calculated, resulting in a total of 100 cases in both the experimental and control groups.

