### Purpose and hypothesis

The objective of this study was to explore whether AB-GG, Bb-12, and M-16V could contribute to neonatal hyperbilirubinemia treatment by regulating gut flora and metabolic imbalances, as well as reducing phototherapy side effects. We hypothesized that children receiving these three probiotics would exhibit a lower incidence of phototherapy side effects. Additionally, we speculated that the experimental group's fecal samples would demonstrate higher diversity and richness in intestinal microbiota compared to the control group. Moreover, we anticipated differences in the dominant bacteria, related metabolites, and metabolic pathways between the experimental and control groups.

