## Methods

### Trial design

The study was designed as a randomized, single-blind trial with an allocation ratio of 4:1. (AB-GG combined with phototherapy, Bb-12 combined with phototherapy, M-16V combined with phototherapy, all of the above probiotics combined with phototherapy, or phototherapy alone). The trial was registered at http://www.chictr.org.cn/index.aspx (registration number: ChiCTR2000036013) (24) before enrolling the first participant. Any significant modifications to the trial will be updated on the mentioned website.

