### Randomization

(1)The randomized scheme of this experiment will be as follows: 100 cases are planned to be enrolled and divided into 5 groups: C0 (pure phototherapy group), T1 (treatment group 1), T2 (treatment group 2), T3 (treatment group 3) and T4 (treatment group 4), with 20 cases in each group.(2)The random system parameters will be set as follows:
•Random system: Taimei Medical eBalance random system•Random method: block random•Block length: 5•Number of blocks: 20•Random number: P001–P100.

The random operation steps would be as follows: The random-related parameters are determined according to the project's random scheme. The eBalance stochastic system is configured according to random parameters. The eBalance random system generated a random grouping table according to the configuration (calling SAS software). The eBalance random system exported the random grouping table.

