### Statistical analysis and bioinformatics analysis

In SPSS software (version 22.0), chi-square distribution and mean value analysis will be used to analyze the characteristics of subjects. The Mann-Whitney test will be used to compare differences between groups, and the Wilcoxon test will be used to analyze differences in alpha diversity. There are five main steps in bioinformatics analysis:

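### Alpha, power and 20 per group are set for one two-group test, but four probiotic arms share one control and the text does not say which contrast decides

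*Protocol article*

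**What the plan says.** Sample size takes from a literature review that "the general incidence of such side effects is approximately 47" per cent, and aims to "reduce this incidence to about 10% by adding the appropriate combination of probiotics". It sets one error rate and one power, "with a type I error of 0.05 and a power of 0.8", and concludes: "Using a difference test for two-sample ratios, a sample size of 20 cases per group was calculated". Five groups of that size make 100.

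Randomization describes a control (C0) and four treatment groups (T1–T4), "with 20 cases in each group". Allocation concealment identifies T1 to T3 as the three single strains and T4 as all three together, each with phototherapy. Trial design says "The study was designed as a randomized, single-blind trial with an allocation ratio of 4:1" and then lists the same five arms.

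Purpose and hypothesis says "We hypothesized that children receiving these three probiotics would exhibit a lower incidence of phototherapy side effects", and goes on to speak of one experimental group against one control group. Endpoints makes a significant reduction in side-effect incidence the primary endpoint and names no arm. The statistical analysis section says "The Mann-Whitney test will be used to compare differences between groups" without saying which groups. It also names chi-square, for subject characteristics, and Kruskal-Wallis, for flora and metabolites.

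**The concern.** The stated error and power belong to one test of two groups of 20. The text supports at least three readings of which test that is:

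- **Combination versus control (T4 vs C0).** Sample size suggests this, because the 10% target is tied to the combination.
- **All probiotic arms pooled versus control (80 vs 20).** The 4:1 ratio and the singular experimental group suggest this.
- **Each of T1–T4 versus control.** Five equal arms and a general two-group test between groups suggest this.

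The readings differ in error rate and in power. Under the third, a trial sized and described at 5% gives four chances of a positive result. If a later document corrected for that by splitting alpha, 20 per arm would no longer deliver the stated power. The choice affects whether a positive result for one arm can be reported at the error rate that the article states.

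**Working it through.** **Inputs.** From Sample size: control rate 0.47, target rate 0.10, difference 0.37, alpha 0.05, power 0.80. From Randomization: 20 per arm, four arms sharing one control. Sidedness is not stated. I assume two-sided, because it reproduces the stated size. The 0.05 margin in Sample size is not needed to do so.

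**1. The plan's own figure.** Unpooled normal formula:

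n = [p1(1−p1) + p2(1−p2)] × (z₀.₉₇₅ + z₀.₈₀)² / (p1−p2)²

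- Variance sum: 0.47×0.53 + 0.10×0.90 = 0.2491 + 0.0900 = 0.3391
- (1.960 + 0.842)² = 7.849
- n = 0.3391 × 7.849 / 0.1369 = 19.4, rounded up to 20

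The stated 20 is one two-sided test at the full 0.05. It contains no allowance for further comparisons.

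**2. Family-wise error if any of four tests can win.** Four z-tests sharing one equal-sized control have correlation 0.5. The chance that at least one rejects under the null is

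1 − ∫ φ(x) [Φ(x + 1.96√2) − Φ(x − 1.96√2)]⁴ dx = 15.6%.

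Four independent tests would give 1 − 0.95⁴ = 18.5%, an upper reference.

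The exact version for binary data sums over the control count i: Σ b(i) [1 − (1 − qᵢ)⁴]. Here b is the binomial probability with n = 20, and qᵢ is the chance that one arm's test rejects given i events in the control.

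| Common rate | Chi-square, two-sided | Chi-square, false benefit only | Fisher, two-sided | Fisher, false benefit only |
|---|---|---|---|---|
| 10% | 12.4% | 5.9% | 4.1% | 1.9% |
| 20% | 15.3% | 8.1% | 7.4% | 3.9% |
| 30% | 16.5% | 8.4% | 8.1% | 4.1% |
| 47% | 13.3% | 6.9% | 6.8% | 3.5% |

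The normal approximation for false benefit alone is 7.8%. The reference for one two-sided 0.05 test in one direction is 2.5%.

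**3. What an alpha split would cost.** Bonferroni gives 0.05/4 = 0.0125 per test. Power for 47% against 10% at 20 per arm:

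| Method | Alpha 0.05 | Alpha 0.0125 |
|---|---|---|
| Chi-square, exact | 78% | 55% |
| Fisher, exact | 67% | 42% |
| Plan's unpooled formula | 81% | 63% |

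To keep 80% by the plan's formula at 0.0125: (2.498 + 0.842)² = 11.15, so n = 0.3391 × 11.15 / 0.1369 = 27.6. That is 28 per arm, or 140 in total.

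**4. The pooled reading.** With 80 against 20 and the same rates, exact chi-square power is about 95%. The stated 0.8 therefore fits a comparison of 20 with 20, not the pooled one.

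**The case against.** The strongest reply is that multiplicity rules usually sit in a statistical analysis plan. That plan is not shown, and this is a condensed article. This stands as far as it goes: the absence of an alpha-sharing rule is not the point here. What remains is that the article fixes alpha, power and n on one contrast, leaves that contrast unnamed, and points to different ones in different sections. A later four-way adjustment would leave 20 per arm too small, and a later single contrast would still need these sections brought into line.

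Four stronger readings are tempting, and the documents do not support them:

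- **That the trial's false-positive rate is about 15%.** No sentence says that any arm may declare success. The figure is conditional on that rule and on a test close to its nominal level. It also counts false findings of harm, whereas the primary endpoint is a reduction. With Fisher's test, false benefit is 1.9–4.1%, close to 2.5%.
- **That 4:1 contradicts five equal arms.** 80 probiotic infants to 20 controls is 4:1, and the five arms follow in the same place. It is loose wording.
- **That Mann-Whitney is the only between-group test and is assigned to the primary endpoint.** Chi-square and Kruskal-Wallis are also named, though for other purposes. The Mann-Whitney sentence is general and does not mention side effects.
- **That an alpha split removes most of the power.** It takes chi-square power from 78% to 55%, a real loss, but about 70% of the power remains (55/78).

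It can also be said that Sample size already implies T4 vs C0. That is a fair reading and the basis of the fix, but it is not stated as the deciding test, and the 4:1 wording and the singular experimental group point elsewhere.

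**Conclusion.** The concern holds in conditional form. The article's 5% error and 80% power describe one two-group test, while the design offers four comparisons with a shared control and no stated deciding contrast. If any of four unadjusted two-sided 0.05 tests can win, the family-wise error is about 12–16% with chi-square and about 4–8% with Fisher. Counting only false benefit with chi-square, it is about 6–8% against 2.5%. With one named contrast it remains at the stated 5%.

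These figures assume two-sided tests, 20 evaluable infants per arm, and a common event rate between 10% and 47% under the null. They do not include any effect of the interim efficacy stop or of the open-ended list of side effects. The case for changing the text does not rest on the exact percentage: the sections need to agree on one contrast, preferably before outcomes are examined by arm.

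**What to change.** 1. In Sample size, Endpoints and the statistical analysis section, name T4 (combination) vs C0 as the single deciding contrast at two-sided 0.05. This follows the assumption already made in Sample size.
2. Test T1, T2 and T3 vs C0 as confirmatory only if T4 succeeds, with Holm adjustment across the three. Otherwise label them exploratory.
3. Label the pooled probiotic arms vs control, and strain-versus-strain comparisons, as exploratory.
4. Analyse side-effect incidence with a two-proportion test and report the risk difference with a 95% confidence interval, to match the sizing.
5. Clarify 4:1 as 1:1:1:1:1 across the five arms.

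**Cost.** Wording only; the 100 infants and alpha of 0.05 are unchanged. The price is that a confirmatory single-strain claim depends on T4 succeeding. Other hierarchies would also control the error, but this one fits the stated size. Exact power for T4 vs C0 at 20 per arm is about 77–78% (Boschloo 76.7%, chi-square 78.4%), slightly below the stated 80%, and 67% with Fisher. The choice of test should be stated with that in view.

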### Randomization

(1)The randomized scheme of this experiment will be as follows: 100 cases are planned to be enrolled and divided into 5 groups: C0 (pure phototherapy group), T1 (treatment group 1), T2 (treatment group 2), T3 (treatment group 3) and T4 (treatment group 4), with 20 cases in each group.(2)The random system parameters will be set as follows:
•Random system: Taimei Medical eBalance random system•Random method: block random•Block length: 5•Number of blocks: 20•Random number: P001–P100.

The random operation steps would be as follows: The random-related parameters are determined according to the project's random scheme. The eBalance stochastic system is configured according to random parameters. The eBalance random system generated a random grouping table according to the configuration (calling SAS software). The eBalance random system exported the random grouping table.

### Blinding

The trial is designed to be single-blind. All neonatologists wouldn't be aware of the group assignments throughout the study, while the parents would be aware of their group assignment to the experimental or control groups.

### Allocation concealment

Based on the randomization table, each enrolled subject will be assigned a serial number in order, which will correspond to one of the following groups: C0 (phototherapy only), T1 (M-16V combined with phototherapy), T2 (Bb-12 combined with phototherapy), T3 (AB-GG combined with phototherapy), and T4 (M-16V combined with Bb-12 combined with AB-GG combined with phototherapy).

### Data collection and management

Each subject will be assigned a unique serial number, and the Case Report Forms (CRFs) will be maintained as a subject's admission history. All fecal microbiota and metabolic results will be entered and stored in a qualified electronic database. The raw materials of CRFs and all study data will be stored in a secure cryptographic cabinet within the research center and will only be accessible to the relevant researchers.

### Monitoring

The results obtained through this study may be published in medical journals, but all trial data and recorded information will be kept confidential in strict accordance with the law. The subjects' personal information will be kept strictly confidential and will not be disclosed unless required by the corresponding law or with their explicit consent. When necessary, the administrative department of the government and the hospital's ethical committee may consult the subjects' data in accordance with the regulations, but only after obtaining appropriate ethical and legal approvals.

This study will develop a data security monitoring plan based on the risk level. All adverse events will be documented in detail and properly handled and followed up until they are resolved or stabilized. Serious adverse events will be promptly reported to the ethics committees, competent authorities, initiators, and drug regulators.

### Statistical analysis

Metagenomic sequencing:Sample extraction and detection: (1) Genomic DNA will be extracted from stool samples using the CTAB method. The quality of the DNA will be analyzed using the Agilent Fragment Analyzer 5,400 automatic capillary electrophoresis system. Library construction and quality control: DNA samples that pass the quality control will be randomly sheared using the Covaris ultrasonic breaker to produce fragments with an average length of approximately 350 bp. (2) These fragments would then be purified and amplified using PCR to generate the final library. Library construction will be performed using the NEB Next®Ultra™ DNA Library Prep Kit for Illumina. Sequencing: The index-coded samples were clustered using the Illumina PE Cluster Kit on the cBot Cluster Generation System. The DNA library was then sequenced using the Illumina Novaseq 6,000 platform to generate 150 bp paired-end reads.

### Statistical analysis and bioinformatics analysis

In SPSS software (version 22.0), chi-square distribution and mean value analysis will be used to analyze the characteristics of subjects. The Mann-Whitney test will be used to compare differences between groups, and the Wilcoxon test will be used to analyze differences in alpha diversity. There are five main steps in bioinformatics analysis:
•Data quality control and de-hosting sequence: KneadData software was used for quality control (based on Trimmomatic) and de-hosting (based on Bowtie2) of original data. FastQC was used to test the rationality and effect of quality control before and after KneadData.•Species annotation: Kraken2 and self-built microbial nucleic acid database (screening NCBI NT nucleic acid database and RefSeq whole genome database belonging to bacteria, fungi, archaea, and viruses) would be used to calculate the sequence number of the species contained in the sample, and then Bracken will be used to estimate the actual abundance of the species in the sample.•Common functional database comments: Starting from the quality control and the removal of host gene reads, HUMAnN2 software (based on DIAMOND) will be used to align the reads of each sample to the database (UniRef90). According to the correspondence between UniRef90 ID and each database, we will obtain the annotation information and relative abundance table of each functional database.•Based on the species abundance table and functional abundance table, PCoA and NMDS dimension reduction analysis (only species) and sample clustering analysis will be analyzed to obtain ɑ diversity, β diversity, bacterial symbiosis network results, etc. When grouping information is available, LEfSe biomarker mining analysis and metabolic pathway comparison analysis can be performed to mine the differences in species composition and functional composition between samples, count metabolite content and screen out characteristic metabolites. Mann-Whitney will be used for assessing gut microbiota and metabolites.•Annotation of resistance genes: Starting from the clean reads of removing host genes, DIAMOND software will be used to compare and annotate the quality control of each sample and the reads of removing host genes with the antibiotic resistance gene database CARD, and the abundance distribution of resistance genes could be obtained.•metabolome analysis using the R language MetaboAnalystR package. This package enables the quantification of metabolite content and the identification of characteristic metabolites. MannWhitney U and Kruskal-Wallis tests will be used to analyze differences in gut flora and metabolites between groups.

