### Eligibility criteria

(1)Inclusion criteria: (1) Jaundice index: According to the American Academy of Pediatrics phototherapy guidelines, the jaundice index reaches the phototherapy threshold; (2) age ≤2 weeks; (3) Term infants with 37 weeks ≤ gestational age < 42 weeks and 2,500 g ≤ birth weight < 4,000 g; (4) No prior use of antibiotics or ecological agents before specimen collection; (5) Healthy mothers during pregnancy, with no history of special drug use, and no intake of antibiotics or microecological agents before, during, or after childbirth; (6) Enrolled infants were exclusively breastfed, exclusively formula-fed, or mixed-fed before admission; (7) All enrolled infants had neonatal pathological jaundice as defined by “Practical Neonatology” and required hospital admission solely for phototherapy; (8) Informed consent provided voluntarily.(2)Exclusion criteria: (1) Gestational age <37 weeks or ≥42 weeks; (2) bilirubin levels reaching the exchange blood transfusion standard or elevated direct bilirubin; (3) complications with pneumonia, septicemia, or other diseases; (4) patients with severe immunodeficiency diseases; (5) those with inherited metabolic diseases; (6) congenital biliary malformations or other organ malformations; (7) drug allergies; (8) situations that may warrant exclusion as determined by the researcher, such as a guardian with mental illness or frequent changes in living or working environments, which may result in loss of follow-up.(3)Elimination criteria: (1) Those refusing the use of their newborn information and their stools and blood; (2) During the treatment process, other drugs might be needed to be added because of other diseases, such as the use of antibiotics and micro-ecological agents.(4)Criteria for withdrawal from the study: (1) participants who suddenly refuse stool and blood collection and request to withdraw from the study; (2) severe gastrointestinal symptoms, such as intense vomiting, diarrhea, or abdominal distension, and other adverse events that significantly affect the treatment process during the probiotics intervention; (3) neonates requiring exchange blood transfusion due to the continued worsening of jaundice after active phototherapy; (4) neonates lost to follow-up, unreachable, or unable to return to the study center for visits.

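### Changes in transcutaneous bilirubin, weight and urine output appear to rest on an unadjusted Mann-Whitney test; adjusting for the recorded D0 value and age would cost almost nothing and may add precision

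*Protocol article*

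**What the plan says.** The Endpoints section lists among the secondary endpoints "changes in jaundice (i.e., serum bilirubin, bile acid and transcutaneous bilirubin data" and "changes in urine volume and weight, and vital signs during phototherapy". Table 1, under Study procedure, has a row "Percutaneous bilirubin determination" marked at D0 and at every later visit. Its row "Weight/urine output" is marked at D0 and at every later visit except the day of discharge.

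On tests, the section on statistical and bioinformatics analysis states "The Mann-Whitney test will be used to compare differences between groups". Just before that it says "chi-square distribution and mean value analysis will be used to analyze the characteristics of subjects". Wilcoxon is assigned to alpha diversity, and Kruskal-Wallis to flora and metabolites. No covariate is mentioned anywhere.

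The inclusion criteria read "According to the American Academy of Pediatrics phototherapy guidelines, the jaundice index reaches the phototherapy threshold; (2) age ≤2 weeks", and the Study procedure section ties the phototherapy criteria to the infant's age. The Randomization section describes five groups of 20, allocated in 20 blocks of 5, with no stratification factor.

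**The concern.** Infants can enter at any age from birth to two weeks, on a bilirubin threshold that depends on age, so entry bilirubin is likely to vary with age. Early weight change also plausibly differs between an infant enrolled in the first days and one enrolled near two weeks. Blocks of 5 across five arms balance the numbers per arm, not entry bilirubin or age.

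A rank test on raw change has two weaknesses here. It subtracts the whole D0 value whatever its correlation with the follow-up value, so some avoidable noise remains. It also has no means of allowing for a D0 or age difference that happens to arise between two arms of 20. The bilirubin endpoints matter most, because the stated objective asks whether the probiotics help treat the hyperbilirubinaemia itself, and the Discussion concedes that the sample is small.

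**Working it through.** **The plan's own figure.** The Sample size section gives 20 per group for 47% versus 10%. The two-proportion formula with unpooled variance, two-sided 0.05 and 80% power, reproduces it if the stated 0.05 margin is ignored: (0.47×0.53 + 0.10×0.90) × (1.960 + 0.842)² / 0.37² = 0.3391 × 7.849 / 0.1369 = 19.4, hence 20. This concerns the binary primary endpoint. The article gives no power statement for the continuous endpoints.

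**Inputs for the comparison.** From the document: n = 20 per arm. Assumed, because the documents give no values: rho, the correlation between D0 and follow-up, and k, the D0 SD divided by the follow-up SD s. A two-sided 0.05 level is also assumed, since sidedness is not stated.

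**Variance per infant.**
- Change score: (1 + k² − 2·rho·k)·s²
- ANCOVA on D0: (1 − rho²)·s²
- Difference: (k − rho)²·s², which is never negative. ANCOVA is therefore not less precise in large samples, and the two are equal when rho = k.

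**Power.** A two-sample t-test on change with 20 per arm has 80% power at a standardised effect of 0.909. Dividing 0.909 by the square root of the variance ratio gives the effect size under ANCOVA.

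| k | rho | Variance ratio, ANCOVA/change | ANCOVA power |
|---|---|---|---|
| 1 | 0.3 | 0.91/1.40 = 0.65 | 93.5% |
| 1 | 0.5 | 0.75/1.00 = 0.75 | 89.9% |
| 1 | 0.7 | 0.51/0.60 = 0.85 | 86.0% |
| 1 | 0.9 | 0.19/0.20 = 0.95 | 82% |
| 0.7 | 0.3 | 0.91/1.07 = 0.85 | 86% |
| 0.7 | 0.5 | 0.75/0.79 = 0.95 | 82% |
| 0.7 | 0.7 | 0.51/0.51 = 1.00 | 80% |
| 0.5 | 0.3 | 0.91/0.95 = 0.96 | 82% |
| 0.5 | 0.5 | 0.75/0.75 = 1.00 | 80% |
| 0.5 | 0.7 | 0.51/0.55 = 0.93 | 83% |

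Allowing two degrees of freedom for the covariates lowers these by about 0.1 point. At k = 1, 20 per arm under ANCOVA is worth 20/ratio, or about 31, 27, 24 and 21 per arm on raw change.

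**Check with the planned test.** The table compares t-tests. A simulation used the Mann-Whitney test on change instead (two arms of 20, 4,000 runs, normal data, k = 1, effect 0.8 SD). Power for Mann-Whitney versus ANCOVA was 53% versus 73% at rho 0.3, 66% versus 80% at 0.5 and 87% versus 92% at 0.7. Both were about 100% at 0.9. Adding age, with an assumed effect of 0.3 SD per SD of age, raised ANCOVA from 80% to 84% at rho 0.5. With no treatment effect, the Mann-Whitney test rejected in 4.7% of runs.

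**Chance imbalance.** The difference between two arm means at D0 has SD √(2/20) = 0.316 baseline SD. For any pair of arms, the probability of a gap above 0.3 SD is 34%, and above 0.5 SD is 11%. Given a 0.5 SD gap and k = 1, the change contrast is shifted by (1 − rho) × 0.5 SD, which is 0.35, 0.25, 0.15 and 0.05 SD at rho 0.3, 0.5, 0.7 and 0.9. At rho 0.5 the test's own SE is √(1.00 × 0.1) = 0.316 and the SE given the gap is √(0.75 × 0.1) = 0.274. The probability of a false positive is then P(Z > (1.96 × 0.316 − 0.25)/0.274), about 9%. The four values are about 10%, 9%, 7% and 6%.

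**The case against.** The case on the other side has several sound parts.

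- **Attribution.** The Mann-Whitney sentence names no endpoint, and the later mentions of that test concern flora and metabolites. This stands: applying it to bilirubin, weight and urine is an inference from the absence of any other candidate.
- **Analysis plan content.** Covariates and repeated-measures models are commonly left to an SAP, and one may exist. A reader might infer that the article is at fault for omitting an adjusted analysis. It is not. The point is only that the comparison it does state is unadjusted and could be improved.
- **Validity.** A reader might infer that the planned test gives biased results or too many false positives. The documents do not support that. Allocation is randomised, and the test keeps its level over randomisations. The 6% to 10% figures apply only given a 0.5 SD gap.
- **Use of baseline.** A reader might infer that D0 is ignored. The endpoints are worded as changes, so D0 is used, though with a weight that is generally not the best one.
- **Guaranteed gain.** A reader might take the equal-SD figures as a minimum gain of 5 points or more. That fails if the entry threshold narrows the D0 spread, or if rho is near 0.9, which is plausible for weight over a few days.
- **Importance.** These are secondary endpoints with no stated power, and weight and urine appear in neither the objective nor the hypotheses.
- **Limits of the remedy.** Further phototherapy sessions depend on the course of the jaundice, so later bilirubin reflects differing exposure. Adjusting for D0 and age does not remove that. Age is also not a listed data item, although the eligibility check requires it.

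What survives is that the stated comparison can be improved with values the trial already has.

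**Conclusion.** The point holds as one of efficiency and of balance in the trial as actually randomised, on secondary endpoints. It is not an error of validity. Over the combinations tabulated, the gain runs from none to about 13 points of power against an 80% reference. It is largest with equal SDs and low correlation, and vanishes when the correlation equals the SD ratio. Both quantities are assumptions, because the documents give neither. The conclusion also rests on reading the general Mann-Whitney sentence as covering these endpoints. Since ANCOVA is not less precise than the change score in large samples and the D0 values are already scheduled, the change is worth making even though its benefit cannot be fixed in advance.

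**What to change.** State which analysis applies to change in transcutaneous bilirubin, weight and urine output. Make the main comparison a linear model with the follow-up value as outcome and arm, D0 value and postnatal age at enrolment as covariates. Use either ANCOVA at a named visit or a repeated-measures model over the Table 1 visits. Report adjusted differences of each probiotic arm from C0 with 95% CIs. Keep the Mann-Whitney test as a sensitivity analysis, and fix all this before outcome data are examined.

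The cost is a change of analysis wording. It needs no further infants, visits or samples. D0 values are in Table 1, and age is known from the eligibility check but should be entered as a data item. The small downside is reliance on a model assumption, which the retained rank test covers.
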